### Measures

Demographic information (age, sex, marital status, occupation, education level) and injury history (time of evolution, type of stroke) from all participants will be collected. Whether they have received or are currently receiving any kind of neuropsychological or functional rehabilitation at the moment of joining the study will be also recorded. The information collection method will be a personal interview. A comprehensive neuropsychological battery will be used to assess the participants. This battery is comprised of performance-based measures to assess attention (Conners Continuous Performance, CPT-II) [28], Trail Making Test A and B [29]), memory (Digit Span forward from the Wechsler Adult Intelligence Scale (WAIS-III) [30], Rey Auditory Verbal Learning Test [31]), speed of processing (Digit Symbol-Coding test from WAIS-III), visuoconstruction (Block Design test from WAIS-III), and executive functions (Digit Span backwards and Letter-Number Sequencing from WAIS-III, Stroop Color and Word test [32], Wisconsin Card Sorting Test – computerized version [33], and a Spanish phonemic fluency test – PMR [34]). Administered rating measures (Rating Scale for Attentional Behavior (RSAB) [35]; Prospective and Retrospective Memory Questionnaire (PRMQ) [36]; Behavior Rating Inventory of Executive Function – Adult Version (BRIEF-A)) [37] will be administered alongside the performance-based measures. All these rating measures will be applied to the patient (self-report) and their recruited next-of-kin (informant-report). Finally, a psychological well-being self-rating scale (Hospital Anxiety and Depression Scale [38]), Patient Competency Rating Scale [39], and the Community Integration Questionnaire [40] will be administered. The Hospital Anxiety and Depression scale will be used to detect participants with emotional disorders. The Patient Competency Rating Scale comprises 30 items, spanning a range of everyday situations and behaviors, and for each item, the patient must make judgment about their own level of competency. The Community Integration Questionnaire is a self-rating scale developed to measure community integration that comprises three subscales (home integration, social integration, and productive activities). These rating measures have been used before in other studies involving stroke patients [41–43].

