#### Primary outcome measures

The primary outcome measures are performance-based measures and rating measures of attention, memory, and executive functions. Since they are different cognitive domains, we need to use different measures for attention (two primary outcomes: the CPT-II and RSAB), memory (Rey Auditory Verbal Learning Test, Digit Span forward from WAIS-III, and the PRMQ), and executive functions (Spanish phonemic fluency test – PMR, Digit Span backward, and the Letter-Number Sequencing Subtests from the WAIS-III and the BRIEF-A). CPT-II is a task-oriented computerized assessment of sustained attention; the Rey Auditory Verbal Learning Test assesses short- and long-term verbal memory and recognition; the PMR test assesses capacity of word generation according to an initial letter (P, M and R); the Digit Span forward test measures the span of immediate verbal recall; Digit Span backward and Letter Number assess working memory; and the RSAB comprises 14 items aimed to identify attentional difficulties on daily routines. The PRMQ includes 16 items, and was designed to evaluate prospective and retrospective memory in the short and long term. The BRIEF-A is designed to assess executive function behaviors on day-to-day activities.

In order to reduce the number of analyses, we will create composite cognitive indices – one for attention, another for memory, and another for executive functions, using sub-scores from the various performance-based measurements of the primary outcome. Composite cognitive indices will include sub-scores on CPT-II, namely number of omissions, number of commissions, and hit of response for attention; sub-scores on Rey Auditory Verbal Learning Test (Trials 1–5 recall, long-delay free recall and recognition) and Digit Span forward from WAIS-III (immediate recall of a series of numbers) for memory; and scores on Spanish phonemic fluency test – PMR (phonemic word fluency), Digit Span backward from the WAIS-III (immediate recall of a sequence of numbers in reverse order in which it was presented), and Letter-Number Sequencing Subtests from the WAIS-III (recall of progressively longer lists of intermixed letters and numbers in alphabetical and then numerical order) for executive functions.

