#### Statistical analysis

##### Analysis

Data analysis will be based on the intention-to-treat principle, which means that all participants who were randomized will be included in the final analysis, regardless of their adherence to any of the interventions. To avoid the problems derived from missing data (no attendance to neuropsychological assessments), blank spots will be filled with missing data imputation technique last value carried forward.

In order to detect changes in the variables recorded for the primary outcome and secondary outcome, a within-subject comparison pre-/post-intervention in both groups after both interventions will be made, as well as comparisons between groups (group A and group B).

Our null hypothesis is that a difference between baseline scores (A1 for group A and A3 for group B) and scores post-treatment (A2 for group A and A4 for group B) will not be significantly different from zero. Therefore, the Kolmogorov–Smirnov test will be used to examine the data for normality, and either ANOVA (parametric test) or Kruskal–Wallis (non-parametric test) will be used to analyze the measurements. A significance level of 95% will be used (*P* < 0.05 cutoff). Demographic (age, sex, years of education) and etiologic characteristics (ischemic stroke or hemorrhage) will be described using descriptive statistics for each group (group A and group B). The Bonferroni method will be applied to adjust the overall level of significance for multiple outcomes.

Alternatively, composite indices will be created by transforming raw neuropsychological test scores into z scores using published normative data. Domains will be created by averaging the z scores for each test within the domain (M = 0; SD = 1). This system has been used before in similar studies [44, 45].

If the sample size of this pilot study allows, a longitudinal mixed model will be applied.

Data analysis will be performed by an analyst outside the study with the statistical analysis software R and appropriate packages (“lmm” and “psych”) [46].

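### Bonferroni is valid for the multiple outcomes, but Holm's step-down procedure gives the same familywise control and never rejects less: a cheap improvement, not the correction of an error

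*Protocol article*

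**What the plan says.** The Analysis section of the Protocol article sets the error level ("A significance level of 95% will be used", which its P < 0.05 cutoff shows to mean 5%) and then the adjustment: "The Bonferroni method will be applied to adjust the overall level of significance for multiple outcomes". It does not say how many tests share that 5%.

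The section on primary outcome measures names nine:

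- Attention: "two primary outcomes: the CPT-II and RSAB".
- Memory: "memory (Rey Auditory Verbal Learning Test, Digit Span forward from WAIS-III, and the PRMQ".
- Executive functions: the phonemic fluency test, then "Digit Span backward, and the Letter-Number Sequencing Subtests from the WAIS-III and the BRIEF-A".

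The Measures section adds a second reporter for the scales: "All these rating measures will be applied to the patient (self-report) and their recruited next-of-kin (informant-report". The primary outcome section also plans to shrink the set: "In order to reduce the number of analyses, we will create composite cognitive indices", one per domain, built from the performance tests. The Analysis section presents these composites as an alternative. The Sample size section describes an explorative pilot with a target of 40 participants and makes no power claim.

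**The concern.** Single-step Bonferroni holds every test to 0.05/m, however many of the other hypotheses have already been rejected. Holm starts at the same threshold and relaxes it after each rejection. It needs no further assumption, so in terms of testing Bonferroni is dominated.

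The trial's hypothesis makes this relevant. The Discussion hopes for benefit in attention, memory and executive functions together, and broad benefit is where stepping down helps most. With about 40 patients, some measures that truly respond could fail to reach significance under Bonferroni and reach it under Holm, with no loss of error control. What is at stake is the second and later findings, not the first.

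**Working it through.** The plan gives no power, effect size or per-test level, so there is no figure of its own to reproduce. The check has five steps.

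**1. Size of the family.** Named measures: 2 + 3 + 4 = 9. Counting the three rating scales for both reporters: 9 + 3 = 12. Three composites plus three rating scales: 3 + 3 = 6. Composites alone: 3.

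**2. Validity of Bonferroni at m = 9.** The per-test level is 0.05/9 = 0.00556. Familywise error under independence is 1 − (1 − 0.00556)^9 = 4.89%, against 1 − 0.95^9 = 37.0% with no adjustment. The stated method does its job.

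**3. Holm at m = 9.** Order the p-values and compare the i-th smallest with 0.05/(9 − i + 1), stopping at the first failure. The thresholds are 0.00556, 0.00625, 0.00714, 0.00833, 0.0100, 0.0125, 0.0167, 0.025 and 0.05. None is below Bonferroni's flat 0.00556, so Holm cannot reject less.

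**4. Size of the gain.** Assumptions, none from the document: two-sided paired t tests on 40 within-person contrasts, equal correlation of 0.4 between measures, equal effects on the measures that respond. Average power per truly responding measure, by simulation:

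| Scenario | Effect (SD) | Bonferroni | Holm | Gain (points) |
|---|---|---|---|---|
| 3 composites, all real | 0.5 | 74.2% | 82.5% | 8.3 |
| 3 composites, all real | 0.4 | 51.8% | 60.0% | 8.2 |
| 6 tests, all real | 0.5 | 64.6% | 76.5% | 11.9 |
| 9 measures, all real | 0.5 | 59.4% | 72.5% | 13.1 |
| 9 measures, all real | 0.4 | 35.7% | 44.8% | 9.1 |
| 12 tests, all real | 0.5 | 55.2% | 68.8% | 13.6 |
| 9 measures, 3 real | 0.5 | 59.5% | 61.6% | 2.1 |
| 9 measures, 3 real | 0.4 | 36.3% | 37.5% | 1.2 |
| 9 measures, all real | 0.2 | 5.7% | 6.5% | 0.8 |

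A between-group contrast with 20 per group shows the same pattern (normal test statistics, correlation 0.5, nine measures all real). At 0.8 SD average power goes from 40.4% to 49.7%, a gain of 9.3 points. At 0.5 SD it goes from 11.7% to 14.3%, a gain of 2.6 points.

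**5. What Holm does not change.**

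- *Power to reject at least one hypothesis.* Both methods make a first rejection only if the smallest p-value is at or below 0.05/m. With all nine effects real, this power is 96.6% under both at 0.5 SD and 86.1% under both at 0.4 SD.
- *Conservatism due to correlation.* When no effect is real, familywise error at m = 9 is the same for both methods: 4.9% at correlation 0, 3.9% at 0.5, 3.1% at 0.7 and 1.8% at 0.9.

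**The case against.** The strongest reply is that nothing in the article is wrong. Bonferroni controls the error rate and contradicts no other statement, and the trial is an explorative pilot whose stated use is to plan a larger study. That planning rests on estimates and variances, which Holm leaves untouched. This stands, and it is why the point is only an improvement. It does not remove the point: the article still commits to a familywise adjustment at 5%, and another procedure does that job at least as well in every case.

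A second reply is that the larger gains need every measure to respond. This also stands. The Discussion says only that training could lead to better function, which does not support equal gains on all nine measures, next-of-kin ratings included. With few responders or small effects the gain is close to nothing.

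A third reply is that the chance of finding anything at all does not change. That is correct. But the article treats the domains as distinct ("Since they are different cognitive domains, we need to use different measures for attention"), so it matters which measures respond, and that is where the gain lies.

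Two stronger readings are tempting and not supported. A reader might infer that Bonferroni is fixed over nine or more tests. The article says only multiple outcomes, and it plans composites precisely to have fewer. A reader might also infer that Holm recovers the power that Bonferroni loses because the measures are correlated. It does not: it ignores correlation, and recovering that loss would need a method that uses the joint distribution, such as step-down resampling.

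**Conclusion.** The point holds as an efficiency improvement of low severity. Holm dominates Bonferroni as a testing procedure whatever the family and the dependence; that part needs no assumption.

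The size of the gain does. At effects of 0.4 to 0.5 SD, 40 within-person contrasts and correlation 0.4, it is about 8 points of average power with three composites and 9 to 13 points with nine measures if all effects are real, and about 1 to 2 points if 3 of 9 are real. If all nine effects are 0.2 SD it is under 1 point. The upper figures are a best case, not an expected gain.

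It would be wrong to conclude that the planned analysis is invalid or that the trial is underpowered because of Bonferroni. The article makes no power claim that could be contradicted. The less tidy feature of the same sentence is that the family is not fixed and the composites appear as an alternative. Holm alone would not settle that, so the fix has to name the family too.

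**What to change.** Replace Bonferroni in the Analysis section by Holm's step-down procedure at a two-sided familywise level of 5% over the primary family. State in the same sentence whether that family is the named primary measures or the three composites plus the rating scales, and whether self-reports and informant reports count separately. Report Holm-adjusted p-values next to unadjusted 95% confidence intervals, labelled as such.

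The cost is one revised sentence. No extra data, patients or assessments are needed. Recruitment was still under way when the article was submitted; the change should be made before any outcome data are seen by group. The one statistical downside is that simple simultaneous confidence intervals, which Bonferroni supplies directly, no longer match the adjusted tests.

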**Fig. 2 Fig2:**
[figure not shown]
SPIRIT figure: schedule of enrolment, interventions and assessments

Evaluations will be conducted pre- and post-training by the study examiner. The examiner will be blind to the allocation of participants. Pre-testing will occur immediately before starting training (A1), and post-testing will occur immediately following both experimental and sham interventions (A2/A4) and after the 3-month washout period (A3). A follow-up neuropsychological assessment will be performed 6 months after treatment has terminated (A5).

A study researcher blinded to assessment procedure will perform the randomization of participants using the rand() function of Microsoft Excel software (Microsoft Excel 2010 for Windows), which is considered a good tool of randomization, having passed the Diehard test [20]. Each participant will have a “list entry” in our database, meaning that they will be stratified based on the two variables of interest in our study – sex (male or female) and type of stroke (ischemic or hemorrhagic). The rand() function will then assign random numbers from 0 to 1 to the stratified sample. The random numbers are ordered from lowest to highest and the first half of the list is assigned to group A and the second half to group B. A study researcher will create a letter with the information of the intervention to be performed (GNPT^®^ or ictus.online) for each participant and will place it in a sealed envelope. The examiner will deliver the sealed envelope to each participant when the first and the third neuropsychological examinations (A1 and A3) take place.

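### The primary family is not fixed: composites are firm in one section and only an alternative in another, so the Bonferroni divisor could be 6, 9 or 16

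*Protocol article*

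**What the plan says.** Only the protocol article is at hand. Two of its sections deal with the primary family.

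- **Primary outcome measures.** It states "The primary outcome measures are performance-based measures and rating measures of attention, memory, and executive functions". It names two instruments for attention, three for memory and four for executive functions. It then says "In order to reduce the number of analyses, we will create composite cognitive indices", one per domain, built "using sub-scores from the various performance-based measurements of the primary outcome". RSAB, PRMQ and BRIEF-A are therefore primary but lie outside the composites.
- **Statistical analysis, Analysis.** The variables recorded for the primary and secondary outcomes are to be tested within subjects and between groups, with a cutoff of P < 0.05. "The Bonferroni method will be applied to adjust the overall level of significance for multiple outcomes". The next paragraph begins "Alternatively, composite indices will be created by transforming raw neuropsychological test scores into z scores using published normative data". No divisor is given.

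The Measures section adds that the patient and a next-of-kin each complete the three rating scales, so each scale yields two scores. The Sample size section calls the trial an explorative pilot of 40 participants, 20 per group.

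**The concern.** One section makes the composites the plan; the other makes them an option beside testing each measure. This is more than an omitted detail, because the article addresses the point twice and gives two answers. The same p-value can then count as a success under one reading and a failure under another. An analyst who has seen the results could take the kinder route, and the 5% family error that Bonferroni is meant to give would no longer be assured. The pilot's results are also to be used to size a full trial, so an estimate carried forward from a route picked for its result would tend to be too large.

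A smaller gap sits in the composites. The attention index averages CPT-II omissions and commissions, which are error counts, with a hit-of-response score. The article does not say that the components are put in the same direction first. If they are not, improvements could partly cancel within the index.

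**Working it through.** **The plan's own figure.** The only stated figure is the overall 0.05 ("A significance level of 95% will be used", read as P < 0.05 and taken as two-sided). No number of tests is given, so no per-test threshold can be reproduced. For any single number m fixed in advance, m × 0.05/m = 0.05. With independent tests, 1 − (1 − 0.05/m)^m gives 0.0490 (m = 6), 0.0489 (m = 9) and 0.0488 (m = 16). Bonferroni works for each family taken alone.

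**Counts** (from Primary outcome measures and Measures)
- Performance sub-scores: CPT-II 3 + Rey 3 + Digit Span forward 1 + PMR 1 + Digit Span backward 1 + Letter-Number 1 = 10.
- Rating scores: 3 scales × 2 respondents = 6.
- Named instruments: 2 + 3 + 4 = 9.

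| Reading of the primary family | Tests m | 0.05/m |
|---|---|---|
| 3 composites + 3 ratings (one score per scale) | 6 | 0.0083 |
| 3 composites + 6 ratings (both respondents) | 9 | 0.0056 |
| Named instruments, one score each | 9 | 0.0056 |
| 10 sub-scores + 6 ratings | 16 | 0.0031 |

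The threshold varies by a factor of 16/6 = 2.7. As an illustration, p = 0.007 succeeds only with m = 6, and p = 0.005 succeeds with 6 or 9 but fails with 16. These counts take one test per outcome. The Analysis section plans both within-subject and between-group comparisons, which would enlarge any m if each were counted.

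**Error if two routes stay open.** Each route is run at 0.05, and success on either is claimed.
- Union bound: 0.05 + 0.05 = 0.10.
- Simulation under no effect: 40,000 replicates, 20 per group, two-sided t tests on change, 16 scores. The article gives no correlations, so the values below are assumed.

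| Correlation within / between domains | Composites + 6 ratings (m = 9) alone | 16 scores alone | Either of these two | Either 3 composites only or 16 scores |
|---|---|---|---|---|
| 0 / 0 | 0.0472 | 0.0497 | 0.0744 | 0.0902 |
| 0.3 / 0.1 | 0.0493 | 0.0472 | 0.0706 | 0.0833 |
| 0.5 / 0.3 | 0.0445 | 0.0440 | 0.0610 | 0.0708 |
| 0.7 / 0.5 | 0.0376 | 0.0356 | 0.0483 | 0.0572 |

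A second simulation, also with assumed correlations, gave about 4 to 7% and about 5 to 9% for the last two columns. The last column is an upper comparison only, because a family of three leaves out the primary ratings.

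**The case against.** The strongest reply is that nothing has gone wrong yet. Bonferroni holds for whichever family is fixed beforehand, and no sentence says that the route will be chosen after looking at results. An analysis plan that is not shown may settle the family, and divisors are commonly left to such a plan. The trial is also an explorative pilot sized from a guideline range, with no power claim to defend. All of this stands and limits the weight of the point. It does not remove the conflict, since an analysis plan would have to depart from one of the two published statements.

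Three stronger readings are tempting, and the article does not support them.

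- A reader might infer that the stated error control fails outright, or that the family may shrink to three tests. The first needs a post hoc choice or a double claim that the article does not announce. The second drops the rating scales, which the Abstract and Primary outcome measures make primary and which the Discussion presents as a deliberate measure of daily functioning.
- A reader might infer that the ratings are unblinded, because a researcher will "create a letter with the information of the intervention to be performed (GNPT^®^ or ictus.online) for each participant". The letter names a platform; it does not say which one is the sham. The sham's interface is designed to look similar, and the relatives' access to the letter is not described. Nor does this bear on the divisor.
- A reader might infer that the CPT-II error scores will be averaged unreversed. The article says only that scores become z scores from published norms. An attention index that ran wholly in the opposite direction would not alter its own two-sided test. What stands is that the direction within the index should be stated.

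**Conclusion.** The point holds as an inconsistency that leaves the primary family and its divisor open. Across the readings that keep the ratings primary, the threshold lies between 0.0083 and 0.0031. The overall 0.05 is not guaranteed, which is weaker than saying that it is lost: an excess arises only if the route is picked after seeing data or both are claimed. It is then bounded by 0.10 for two routes. Simulated error is about 4 to 9% overall and about 4 to 7% for composites plus ratings against all 16 scores, so with highly correlated scores there may be no excess at all. The simulated figures rest on assumed correlations and on one between-group test per outcome; the counts and the bound do not depend on the correlations. For an explorative pilot the weight is moderate, but the trial has chosen a formal error level and should say what it applies to.

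**What to change.** Before analysis:

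1. Delete *Alternatively* and name one primary family: the three performance composites plus RSAB, PRMQ and BRIEF-A, stating whether the patient's score, the informant's score or both count.
2. Control that family at overall 0.05 by Holm and state the number of tests: 6 with one score per scale or 9 with both respondents, given one designated comparison per outcome. Holm is never less powerful than Bonferroni; Bonferroni with a stated divisor would also cure the ambiguity.
3. Make the individual performance sub-scores secondary.
4. State that CPT-II error scores are reversed where needed, so that all components of the attention index point the same way before averaging.

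Whether the ratings stay primary is the sponsor's choice, provided that it is fixed in advance and the number of tests follows from it. The change costs wording only; the downside is that the individual sub-scores lose primary status.
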